### Methods in analysis to handle protocol non-adherence and any statistical methods to handle missing data {20c}

The data will be analysed based on the full analysis set (FAS), per-protocol set, and safety set. FAS analysis is the basic principle of intention-to-treat, including all the enrolled patients in the trial. Analysis will follow intention-to-treat principles with patients analysed according to randomisation and irrespective of actual use or compliance with the algorithm. The per-protocol analysis is the subset of FAS analysis, which just includes patients who finish the trial completely. The safety set analysis is the set of patients who receive the treatment and have safety assessment. Missing values will be addressed by multiple imputation, having appropriately explored the missingness mechanism and in accordance with good practice.

### Plans to give access to the full protocol, participant-level data, and statistical code {31c}

Final data of the trial that support the findings of this study are available from the corresponding author upon reasonable request.

## Oversight and monitoring

### Composition of the coordinating Centre and trial steering committee {5d}

The trial steering committee consists of four members, who will hold meetings monthly and audit the trial. [name], as the primary investigator, will be responsible for the overall management of the trial. [name] has expertise in clinical trials and will be the clinical lead in the trial. [name] has expertise in biological specimen management and will lead the biobank platform for the trial. [name] is an expert who will ensure the quality control of CQCQD.

### Composition of the data monitoring committee, its role and reporting structure {21a}

An Independent Data and Safety Monitoring Committee (IDSMC) consists of two clinical experts and one statistician, who are responsible for overseeing the safety and quality of the data. The committee is independent and has no competing interests with the research. The IDSMC will consider protocol adherence, trial withdrawal, and safety monitoring and will make recommendations for continuation of the trial.

### Adverse event reporting and harms {22}

Adverse events (AEs) are defined in accordance with the National Cancer Institute-Common Terminology Criteria for Adverse Events. The common aberrations in symptoms, signs, and laboratory values due to the severity of the underlying disease and the impact of standard therapies will not necessarily constitute an AE unless they require significant intervention or are of concern in the investigator’s clinical judgement. If severe adverse events (SAEs) happen that threaten the patients’ safety, the researcher should stop the study at once, cancel the blinding, and take any measures to rescue the patients’ lives who experience SAE.

All details of any AE/SAE will be documented and reported during the treatment and the follow-ups. Furthermore, SAE will be reported to the principal investigator and the BREC immediately to decide whether the patient should withdraw from the trial.

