## Interventions

### Explanation for the choice of comparators {6b}

#### Conventional treatment regimen

All patients will receive standard treatment according to recently published guidelines [7, 8], including fluid therapy, nutritional supplementation, routine medical treatment such as proton pump inhibitors, analgesia and antibiotics as indicated, organ supportive therapy, and ERCP if necessary. Nasogastric and annal tubes will be used for patients with intra-abdominal hypertension (IAH) or abdominal compartment syndrome (ACS). For patients with persistent ACS or new-onset organ failure, percutaneous drainage of ascites and surgical abdominal decompression will be considered [37, 38]. When pancreatic infection occurs, either a surgical or endoscopic step-up approach considering the location of the necrotic collection and the technical availability will be applied.

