#### Study herbal formulation

The prescription of CQCQD was developed by this research team and standardised to contain 13 Chinese medicines, the contents of which can be found in Table 1.

**Table 1 Tab1:** The ingredients list of standardised Chinese herbal medicine prescription of CQCQD

Ingredients	Latin name	Plant name	Weight (g)
Dahuang	*Rhei Radix et Rhizoma*	*Rheum palmatum* L.	15
Houpo	*Magnoliae Officinalis Cortex*	*Magnolia officinalis* Rehd. et Wils.	15
Zhizi	*Gardeniae Fructus*	*Gardenia jasminoides* Ellis	15
Zhuyechaihu	*Bupleuri Radix*	*Bupleurum chinese* DC.	15
Huangqin	*Scutellariae Radix*	*Scutellaria baicalensis* Georgi	15
Chuanxiong	*Chuanxiong Rhizoma*	*Ligusticum chuanxiong Hort.*	15
Honghua	*Carthami Flos*	*Carthamus tinctorius* L.	10
Zhishi	*Aurantii Fructus Immaturus*	*Citrus aurantium* L.	15
Yanhusuo	*Corydalis Rhizoma*	*Corydalis yanhusuo* W. T. Wang	15
Muxiang	*Auklandiae Radix*	*Aucklandia lappa* Decne.	15
Chishao	*Paeonia Radix Rubra*	*Paeonia veitchii* Lynch	15
Gancao	*Glycyrrhizae Radix et Rhizoma*	*Glycyrrhiza uralensis Fisch.*	3
Mangxiao	*Natrii Sulfas*	Na_2_SO_4_ • 10H_2_O	30

Due to the absence of a positive control drug for AP and the difficulty in preparing a placebo for the decoction, we will utilise a low-dose arm administering 10% CQCQD of similar colour and odour by adding dextrin and colourant, which intend to mimic the placebo group as a control [39]. Generally, the selection of control in a pragmatic trial is usually based on conventional or standard treatment, and placebo is not routinely used as a control. However, the placebo is applied in our trial for following the reasons: (1) The standard treatment for AP including analgesia and fluid therapy is needed in all AP patients and cannot be used only in the control group. (2) Placebo control is designed in our trial to minimise the expectant effect of participants and researchers, as well as to control bias caused by psychological factors from researchers, participants, and evaluators.

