### Intervention description {11a}

#### Administration of randomised drugs guided by the AGI-based algorithm

The AGI grade has been widely used to assess gastrointestinal injury in patients with acute critical illness [11, 40]. Evidence has shown that the AGI grading system is useful for identifying the severity of gastrointestinal dysfunction/failure in AP [41]. In our study, the participants will receive randomised drugs guided by the AGI-based algorithm (Fig. 1).Initiation: If the Bedside Index of Severity in Acute Pancreatitis (BISAP) score or Glasgow Criteria System (GCS) < 2 at allocation [42, 43], the patients will empirically receive CQCQD or placebo 200 mL oral intake (or intragastric infusion) and enema, 3 times a day. If the patients have a BISAP/GCS score ≥ 2 at allocation, they will be required to receive urethral catheterisation to monitor intra-abdominal pressure (IAP) every 4 h, which is the key index in AGI grade. The dosage and frequency of decoction is determined by AGI grading according to the following criteria: (1) if AGI grade = 1, 200 mL CQCQD or placebo is administered orally (or intragastrical infusion) and enema, 3 times a day; (2) if AGI grade = 2, CQCQD or placebo is given 100 mL orally (or intragastrical infusion) and 200 mL enema, every 6 h; (3) if AGI grade = 3, CQCQD or placebo are given 100 mL orally (or intragastric infusion) and 200 mL enema, every 4 h; (4) if AGI grade = 4, CQCQD or placebo is given 100 mL orally (or intragastric infusion) and 200 mL enema, every 2 h. If the patient with a BISAP/GCS score ≥ 2 at allocation rejects urethral catheterisation, the initial administration of the randomised drug is in accordance with AGI grade 1, and the conditions will be reassessed for further judgement.Continuation: AGI grade is evaluated daily at 7–8 am by the researchers. The dosage and frequency of CQCQD or placebo are determined by the corresponding AGI grade at the time points.Termination: CQCQD or placebo is administered for at least 5 days and no more than 14 days. IAP monitoring will be terminated if it is less than 15 mmHg for two consecutive days. CQCQD or placebo will be terminated, if AGI grade < 1 for two consecutive days, or normally oral refeeding without discomfort. Other conditions will be determined by clinical treatment leaders and principal investigators.The upgrade principle for patients with AGI grade 1 initially or who reject urethral catheterisation: (1) the aggravation of abdominal distension and constipation; (2) the occurrence of new organ dysfunction; (3) the deterioration of the original organ function; and (4) other conditions will be assessed and determined by clinical treatment leaders and principal investigators.

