
### Criteria for discontinuing or modifying allocated interventions {11b}

The patients are withdrawal if they meet any of the following criteria:Having manifestations of gastrointestinal perforation, bleeding, mechanical ileus, severe haemorrhoids, and anal fissure which require restricted fast and enema.Quitting voluntarily.Adverse medical events occurring during the study, such as severe hypernatremia, intolerance to critically worsening conditions, or other reasons as judged by the investigators, which might make the patient unlikely to complete the study.

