#### Secondary outcome measurements

I.Secondary outcomes during the index admissionThe occurrence of new-onset of any organ failure (SOFA score for respiratory, cardiovascular, or renal system ≥ 2 points) or new-onset of POF (organ failure lasts > 48 h). New onset is defined as events that occur after randomisation and not present 24 h before randomisation.Cumulative levels of C-reactive protein (CRP) on days 1, 2, 3, 5, 7, 14, 21, and 28 after admission.Levels of albumin, procalcitonin, interleukin-6 (IL-6), and neutrophil count on day 0, day 3, day 5, day 7, and day 14.Daily visual analogue scale (VAS) score of pain [45].Daily Pancreatitis Activity Scoring System (PASS) score within the 1st week after enrolment [46].Duration (days) of Systemic Inflammatory Response Syndrome (SIRS ≥ 2 points) [47].Duration (days) of fasting.The requirement of the anal tube.The requirement of prokinetic agents.Duration (days) of gastrointestinal decompression.Duration (days) of IAH and ACS.The receipt of respiratory support and renal replacement therapy.Length of intensive care unit (ICU) stays.Local pancreatic injury by contrast-enhanced computerised tomography (CECT) on days 7 and 14.Potential safety signals.Length of hospital stay.In-hospital cost.II.Secondary outcomes within 26 weeks after enrolmentThe requirement for catheter drainage or necrosectomy.Infected pancreatic necrosis.All-cause mortality.Self-report health situation by five-level EuroQol five-dimensional (EQ-5D-5L) [48].

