## Assignment of interventions: blinding

### Who will be blinded {17a}

All the patients, researchers, and statisticians in this clinical study will be blinded to the treatment assignment and unaware of the actual medications.

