### Data management {19}

The researchers involved will receive restricted training to ensure that the study process is detailed. Data collection will use a CRF and include source-verifiable data from patient records. CRF will be anonymised and contain no individual patient-identifiable information. Paper copies of the CRF will be stored in a locked cabinet in the Chief Investigator’s office in West China Hospital. All data will be input by the primary investigator or nominated investigators approved by the primary investigator, and a double check will be performed by the research coordinator.

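### The adverse event rule permits, but does not require, a non-severe sodium rise to go unrecorded when a blinded investigator attributes it to pancreatitis or standard care, it needs no significant intervention and it is not of concern

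*Protocol article*

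**What the plan says.** The rule is in the protocol article, Adverse event reporting and harms {22}. AEs follow CTCAE, with an exception for common changes in symptoms, signs and laboratory values that stem from disease severity or from usual care. The operative words are: "the underlying disease and the impact of standard therapies will not necessarily constitute an AE unless they require significant intervention or are of concern". The concern meant is the investigator's own clinical judgement. Full documentation is then promised for whatever counts as an AE or a serious AE.

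Five other places bear on sodium:

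- Study herbal formulation, Table 1, lists 30 g of sodium sulphate decahydrate in the formula. The control is a "low-dose arm administering 10% CQCQD of similar colour and odour", made up with dextrin and colourant.
- The AGI-based algorithm gives the same volume and frequency in both arms at each grade, for example "if AGI grade = 1, 200 mL CQCQD or placebo is administered orally (or intragastrical infusion) and enema, 3 times a day".
- Criteria for discontinuing or modifying allocated interventions {11b} gives as a ground for withdrawal "Adverse medical events occurring during the study, such as severe hypernatremia".
- Conventional treatment regimen states: "All patients will receive standard treatment according to recently published guidelines [7, 8], including fluid therapy".
- Who will be blinded {17a} states that patients, researchers and statisticians "will be blinded to the treatment assignment and unaware of the actual medications".

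Secondary outcome measurements lists "Potential safety signals" and names no laboratory value.

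**The concern.** The exception turns on cause: the investigator must decide whether a laboratory change comes from the disease or usual care. For most values in acute pancreatitis that is a sensible way to keep the AE list readable. Sodium differs because the test product is itself a sodium source, the control contains far less of it, and the protocol already foresees hypernatraemia in its severe form.

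A mild or moderate rise in a patient who has pancreatitis, is receiving fluids and is taking a blinded decoction has three candidate causes. The investigator cannot reliably choose among them at the bedside. Randomisation can separate the decoction from the other two without anyone judging cause, but only if the rises are counted first.

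At stake is the completeness of one foreseeable item within a listed secondary outcome. Where the count depends on individual judgement, it may also vary between investigators.

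**Working it through.** The protocol gives no figure on this point to reproduce. The check has two parts: what the rule lets through, and how large the sodium contrast is.

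**1. What the rule lets through.** A sodium rise may go unrecorded as an AE only if all of these hold:

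- (a) it counts as a common aberration;
- (b) it is attributed to disease severity or standard therapy;
- (c) it needs no significant intervention;
- (d) it does not concern the investigator.

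Even then the wording is permissive, so omission is allowed and not required. Severe hypernatraemia is treated as an adverse event under {11b}. What remains exposed is the non-severe rise. Whether such a rise is common in the sense of (a) is not stated, so two investigators could answer differently.

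**2. Sodium per prescription.** The input is 30 g of Na2SO4·10H2O (Table 1).

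- Molar mass: 2 × 22.99 + 32.06 + 64.00 + 10 × 18.015 = 322.19 g/mol.
- CQCQD: 30 / 322.19 × 2 = 0.186 mol, or 186 mmol of sodium.
- Control at 10%: 18.6 mmol, assuming the sodium sulphate is diluted along with the other ingredients.
- Gap: 186.2 − 18.6 = 167.6 mmol per prescription. Ratio: 10.

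**3. Sensitivity to excipients.** The sodium content of the dextrin and colourant is not given. If they add x mmol per prescription-equivalent to the control, the ratio is 186.2 / (18.62 + x):

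| x (mmol, assumed) | ratio |
|---|---|
| 0 | 10.0 |
| 1 | 9.5 |
| 2 | 9.0 |
| 5 | 7.9 |

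**4. Does the ratio hold at every grade?** Daily volume is (oral + enema) × doses per day. Grade 1 is read as 200 mL by each route.

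| AGI grade | calculation | mL per day, either arm |
|---|---|---|
| 1 | (200 + 200) × 3 | 1200 |
| 2 | (100 + 200) × 4 | 1200 |
| 3 | (100 + 200) × 6 | 1800 |
| 4 | (100 + 200) × 12 | 3600 |

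At a given grade the volumes are the same in both arms, so the ratio per prescription carries over to the sodium given. Prescribed volume is highest at grade 4, where gut injury is worst and where a sodium rise may most easily be put down to the disease.

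**5. What cannot be computed.** The volume that one prescription yields and the share of sodium absorbed are not given. No daily sodium load, hypernatraemia rate or number of missed events follows from the protocol.

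**The case against.** The strongest reply is that the text contains no error. CTCAE is the starting definition, the exception is permissive, and it has two safeguards. Naming severe hypernatraemia as a withdrawal ground alerts investigators to sodium, so a rising value may well count as being of concern. Relevant concomitant care {11d} requires added drugs and therapies to be entered in the case report form, so treated cases leave a trace, and an independent committee oversees safety. A list of laboratory values of special interest is often kept in a full protocol or analysis plan, and the schedule in Table 2 is not visible here.

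Much of this stands. It rules out three stronger readings that a reader might infer:

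- That the protocol excludes hypernatraemia from AE reporting. It does not; it leaves the non-severe form to judgement.
- That sodium is not measured. Nothing says so, and a withdrawal criterion based on severe hypernatraemia presumes measurement.
- That the safety comparison is tilted towards one arm. Attribution is blinded, so the likely effect is under-recording in both arms. A selective loss of background cases alone would require investigators to tell them from drug-caused cases, which blinding makes unreliable.

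The reply does not remove the narrow point. The attribution rule is stated in the article, so this is not a matter of detail left to another document. For this one value, blinded attribution is a weaker basis than counting every rise.

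**Conclusion.** The point holds in limited form, as an inexpensive improvement and not as a flaw in the trial's main conclusions. The rule leaves recording of a foreseeable laboratory effect to a judgement of cause that blinded investigators cannot make reliably. The likely consequence is an incomplete AE count for non-severe hypernatraemia in both arms, of unknown size.

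The contrast in composition is about 186 against 19 mmol of sodium per prescription: tenfold if excipients add no sodium, and roughly eightfold if they add 5 mmol. This rests on the control being a uniform 10% preparation given at the same volumes. It also rests on reading a mild sodium rise as something an investigator could class as a common aberration, which the text leaves open.

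A reader might take the tenfold ratio as evidence that hypernatraemia will be frequent or will differ between arms. It is a ratio of contents and shows neither.

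**What to change.** Keep the general exception in {22}. Make two changes.

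1. Under the safety outcome, specify a comparison between arms of peak serum sodium, or worst CTCAE sodium grade, during treatment up to day 14 (the longest permitted treatment). Include all treated patients and use recorded values whatever cause was assigned. Data management {19} already provides the route: "Data collection will use a CRF and include source-verifiable data from patient records". A peak depends on how often sodium is measured and for how long, so report the number of measurements and the days on treatment by arm beside it.
2. Add one sentence to {22}: hypernatraemia of any CTCAE grade is recorded as an AE regardless of attributed cause.

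The second change should not carry the comparison. Recruitment began on 1 August 2020 (Trial status), so AE labels would mix two recording rules; the sodium values would not.

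The cost is an amendment submitted to the ethics committee under {25}, transcription of sodium values, and a longer AE list that will include disease-related rises.

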## Introduction

### Background and rationale {6a}

Acute pancreatitis (AP) is an inflammatory disorder of the pancreas [1]. The common causes of AP such as gallstones, alcohol, hypertriglyceridaemia, endoscopic retrograde cholangiopancreatography (ERCP), and various drugs trigger self-digestion of acinar cells and induce local and systemic inflammation. It has an increasing prevalence with an overall incidence of over 34 affected cases per 100,000 person-years [2]. Most of the patients are uneventful and recover from mild disease (mild acute pancreatitis, MAP), or pull through local complications or transient organ failure defined as moderately severe acute pancreatitis (MSAP). Approximately 15–20% of patients manifesting persistent organ failure (POF) are defined as severe acute pancreatitis (SAP) [3], which are at risk of multiple organ failure (MOF) and the mortality can be up to 50% [4, 5]. Despite the global socioeconomic burden of disease, currently, there are no specific and effective therapeutic agents available to treat AP [6]. According to published guidelines [7, 8], supportive measures, such as analgesia, fluid therapy, nutritional supplementation, and organ support, remain the primary management modalities for AP patients.

Traditional Chinese medicine (TCM), which contains abundant multiple-target biologically active substances, has been broadly used in many countries and regions. Gastrointestinal dysmotility or dysfunction/failure, one of the common and complex complications in AP [9–11], is widely accepted as an important role in the pathogenesis of systemic inflammation and MOF [12–14]. Most TCM herbal formulas, such as dachengqi decoction [15, 16], qingyi decoction [17, 18], and rhubarb [19, 20], are used as an important “gut-centred” therapeutic strategy in the early treatment of AP [21]. Based on TCM theories, we summarised that the key pathogenesis of SAP-MOF is the invasion of “evil heat” to the organs, and its treatment requires “clearing heat, removing toxin, and purging the bowel” in clinical practice [22, 23]. Systematic reviews and meta-analyses of observational studies and trials with small sample sizes have demonstrated the effectiveness of rhubarb-contained TCM in reducing inflammatory markers, organ failure, local complications, and mortality, albeit the included clinical trials are of low quality [24–26].

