### Procedure for unblinding if needed {17b}

The study blinding will only be broken in a medical emergency when the treating physician believes that the administration of the study drug is associated with the emergency.

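### The unblinding and harms sections give incompatible code-break rules, so knowledge of the arm could reach staff for some patients with serious organ failure who remain in the analysis

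*Protocol article*

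**What the plan says.** Two sections of the protocol article govern when allocation may be revealed.

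- Procedure for unblinding if needed {17b} sets a narrow condition: "The study blinding will only be broken in a medical emergency when the treating physician believes" the study drug to be linked to it.
- Adverse event reporting and harms {22}: "If severe adverse events (SAEs) happen that threaten the patients’ safety", then "the researcher should stop the study at once, cancel the blinding", and rescue measures follow.

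Section {22} also says which events enter the AE system. Common abnormalities arising from the disease or from standard therapy "will not necessarily constitute an AE unless they require significant intervention or are of concern in the investigator’s clinical judgement". Of what happens next it says: "SAE will be reported to the principal investigator and the BREC immediately to decide whether the patient should withdraw from the trial".

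Four other sections bear on the point:

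- Who will be blinded {17a}: "All the patients, researchers, and statisticians in this clinical study will be blinded to the treatment assignment".
- Plans for assessment and collection of outcomes {18a}: follow-up continues after the study drug is stopped, unless the participant withdraws.
- Section {20c}: patients are analysed as randomised, whatever they actually received.
- Composition of the data monitoring committee {21a}: recommendations on continuing the trial come from the independent committee.

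**The concern.** The word *only* in {17b} excludes any wider ground for unblinding, yet {22} supplies one. The rules differ in trigger (an emergency attributed to the study drug, or any safety-threatening SAE) and in actor (the treating physician, or the researcher). A research team facing a deteriorating patient cannot comply with both.

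This matters more here than in many trials. Predicted mild disease is excluded, so serious organ failure is an expected part of the disease course. If {22} is followed, staff may learn the arm of some of these patients while data on them are still being collected. Several later steps depend on judgement: daily AGI grading by researchers, which sets how the decoction is given; discretionary decisions by the clinical leaders and principal investigators; organ support and prokinetic use, which are also secondary outcomes; and attribution of AEs. The article justifies its placebo control as protection against bias from researchers, participants and evaluators. That protection would be weakened for these patients.

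**Working it through.** The plan states no figure to reproduce. The check is a comparison of text, followed by an illustration of scale.

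**Step 1. The two rules side by side.**

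| | Section {17b} | Section {22} |
|---|---|---|
| Event | Medical emergency | SAE that threatens safety |
| Drug causality required | Yes, in the treating physician's belief | Not stated |
| Who acts | Treating physician's belief decides | Researcher |
| Action | Blind may be broken | Study stopped and blinding cancelled |

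An SAE that threatens safety but is attributed to pancreatitis falls outside {17b} and inside {22}. For that event the two sections give opposite instructions.

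**Step 2. Can a disease-driven event reach the {22} trigger?** Yes, but not automatically. The AE definition sets aside common disease-related abnormalities, then readmits those that need significant intervention or concern the investigator. Organ failure needing ventilation or renal replacement can plausibly be readmitted. It must then also be an SAE that threatens safety.

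**Step 3. Does the unblinded patient still contribute data?** Yes, unless the patient withdraws. Under {22}, withdrawal is decided after the SAE is reported. Under {18a}, stopping the drug does not end follow-up. Under {20c}, analysis is as randomised.

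**Step 4. Who might know the arm afterwards?** The article does not say who is told after a code break, or who scores respiratory SOFA. The independent assessors in Concealment mechanism {16b} are described for interview and screening only. AGI grading is assigned to the researchers in Intervention description {11a}.

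**Step 5. Scale, by assumption only.** The planned total is 248 (Sample size {14}). The article gives no SAE rate for this population. With *f* the assumed share of patients who have a safety-threatening SAE and are unblinded under {22}, the number is *f* × 248:

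| Assumed *f* | *f* × 248 | Patients, about |
|---|---|---|
| 5% | 12.4 | 12 |
| 10% | 24.8 | 25 |
| 15% | 37.2 | 37 |
| 20% | 49.6 | 50 |
| 30% | 74.4 | 74 |

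Under {17b}, only the patients whose emergency the treating physician attributed to the study drug would be unblinded. The article gives no figure for that either.

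**The case against.** The strongest reply is that this is a wording conflict with little demonstrated consequence. Most of its parts have force.

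- *Disease events are screened out.* This is partly right. The AE definition makes inclusion a matter of judgement, and the trigger is narrower than any SAE. It does not exclude serious disease-driven events, so the conflict remains.
- *The primary endpoint state is not the trigger.* This stands. The endpoint is respiratory SOFA of 2 or more, while the eligibility criteria exclude only scores above 3. Patients with a score of 2 or 3 may enrol and accrue endpoint days from admission with no code break.
- *No count can be derived.* This stands. A reader might apply the Background section's 15–20% ("of patients manifesting persistent organ failure (POF) are defined as severe acute pancreatitis (SAP") to 248 and read off 37 to 50 unblinded patients. That figure describes acute pancreatitis in general, and the step also assumes that every case of persistent organ failure is a safety-threatening SAE and is unblinded. The article supports none of these assumptions.
- *Assessment by unblinded staff is an inference.* This stands. The article does not name the SOFA scorers or the recipients of the code, and such detail may sit in a fuller protocol. Part of the respiratory score also rests on objective measurement.
- *Several safeguards already exist.* This is correct. The statistician is blinded ({17a} and {20a}), follow-up continues after the drug is stopped, and analysis is as randomised. These need only be confirmed as applying after a code break.
- *Stopping the study plainly means the patient's participation.* This is the likelier reading, since {22} goes on to ask whether the patient should withdraw. The words do not say so, and read literally they cut across the monitoring committee's role.

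None of these points reconciles the two code-break rules.

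**Conclusion.** The point holds as an internal inconsistency: {17b} and {22} cannot both be followed when a safety-threatening SAE is not attributed to the study drug. Following {22} as written could reveal the arm to staff for some patients with serious organ failure who remain in follow-up and in the as-randomised analysis. Judgement-based decisions and outcomes are the ones exposed; the effect on the measured part of respiratory SOFA may be limited. Neither the direction nor the size of any bias can be established from the article.

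The scale is unknown. The 12 to 74 of 248 rests wholly on assumed shares of 5% to 30% and on every such event being unblinded.

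Two stronger readings should not be adopted. One is that reaching the primary endpoint itself triggers unblinding; the eligibility criteria and the AE definition do not support it. The other is that the sickest patients will have their primary outcome assessed unblinded; the article is silent on who scores it.

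The contradiction depends on none of these numbers and should be resolved.

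**What to change.** Reconcile {17b} and {22} into a single code-break rule. Which clinical circumstances justify a code break, and how the patient is then managed, stays with the investigators. Whatever rule they keep, the text should:

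1. Limit disclosure of the arm to the treating physician who needs it.
2. Keep those who score outcomes and those who grade AGI blinded, as far as existing staff allow.
3. Require a log of every code break, to be tabulated by arm.
4. State that the existing rules on continued follow-up {18a} and as-randomised analysis {20c} apply after a code break.
5. Say whether the instruction to stop the study refers to the individual patient, given that recommendations on trial continuation belong to the monitoring committee {21a}.

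The cost is a wording amendment, submitted to the ethics committee under the protocol's own amendment procedure, and a simple log. Sample size and outcomes do not change. Item 2 is worded to use existing staff, so no extra posts are implied.
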